#### Monitoring recruitment progress

Based on the pilot study recruitment rate,^27^ we plan to recruit the target sample over a 12-month period. We employ a recommended traffic light system (figure 1) to review trial progression at the midpoint of the recruitment period,^62^ with the following actions: proceed if >50% of target achieved; modify recruitment approach if 25%–49% achieved and consider stopping (discuss with funder and TSC) if <25% of target recruited.

### Screening

All trial information materials disseminated via described recruitment pathways, direct women who are potentially interested in taking part to contact the research team via telephone, email or by accessing the trial website/scanning a QR code to submit a secure pro-forma with their contact details.

Site researchers contact women expressing an interest in their area to provide a PIS, privacy notice and copy of the consent form (online supplemental appendix 2) via email or post. Audio versions of the PIS and privacy notice are available on the trial website to increase accessibility (go.qub.ac.uk/SMSstudy). To comply with the Welsh Language Act 1993, Welsh language versions of the PIS and Consent Forms are available on request. Women are given at least 48 hours to consider the information before being contacted again by telephone by the research team to discuss the trial procedures and any queries and then invited to take part. Up to three contact attempts are made to invite all women who expressed an interest in the study for screening. BMI eligibility is initially determined using women’s self-reported height and weight but later measured and verified by the researcher prior to collecting informed consent. Women who are deemed ineligible due to their baby being less than 6 weeks old will be invited for rescreening when they reach 6 weeks postpartum.

### Informed consent and withdrawal

For women meeting the eligibility criteria and willing to proceed with trial participation, a baseline researcher visit is arranged. Home visits are the primary approach to data collection, with women also offered the option of attending another venue if preferred (University building, community venue or their workplace).

Research staff, trained in Good Clinical Practice (GCP) guidelines, obtain written informed consent prior to collecting baseline data. At the baseline visit, women are offered the opportunity to ask further questions and confidentiality of data is explained. Informed consent is then taken. Women are reminded that they have the freedom to choose whether to take part or not. If willing to proceed, women are asked to initial and sign the trial consent form, with optional consent to be invited for telephone interview participation at 6 and 12 months. During the 6-month and 12-month trial visits, women providing this optional consent at baseline are asked if they are still happy to be contacted to take part in a telephone interview. Participants completing telephone interviews are asked to provide their verbal consent for audio recording and for anonymised quotations to be used in trial publications before commencing interviews.

Once consented, participants are advised that they can withdraw from the trial at any time and without giving a reason, should they wish. Withdrawals are documented in the case report form (CRF) along with any reason given for withdrawing. Participants excluded due to pregnancy are given the option to continue receiving the text messages. Anyone choosing this option needs to complete and return a pregnancy form to acknowledge that the messages have not been designed for pregnancy but may be useful after pregnancy. Data collected up to the point of withdrawal are retained for analysis unless the participant specifies otherwise.

### Additional consent provisions for collection and use of participant data and biological specimens

Optional aspects of trial consent include permission to be informed of future follow-up to this trial or other relevant research studies and permission for future data linkage to routinely collected health records for long-term health outcomes (mother and youngest child) which is not within the current trial timeline. No biological specimens are collected.

### Assignment of interventions: allocation

#### Sequence generation

Participants are randomised in blocks of size 4 and randomisation is stratified by site, with the allocation sequence generated in STATA (using ralloc) by an independent statistician.

### Concealment mechanism and allocation implementation

The allocation sequence is sent directly to the platform manager at LSHTM for upload to the secure web-based text message delivery system. After collecting consent and baseline data, site researchers enrol participants using the LSHTM randomisation system linked directly to the text message platform which implements the random allocation sequence by accordingly sending automated intervention or control messages to the participant. Participants become aware of their group allocation when they start to receive the text messages; researchers do not have access to this information.

## Blinding

Researchers responsible for recruitment and collecting outcome data are blinded to group allocation. It is not possible to blind participants, but they are requested not to discuss the text messages they are receiving with researchers at each visit. This worked well in the pilot study with blinding maintained.^27^ All statistical analyses are conducted blinded to group allocation until analyses of the 12 month data point are complete, at which point the randomisation sequence is provided by the independent statistician who prepared it. We record any circumstances in which unblinding has occurred. The trial clerical officer, CI and LSHTM text message system developer are not blind; these individuals see what group individuals are assigned to on the text message system for the purposes of monitoring the intervention delivery and the clerical officer is responsible for preparing the group-specific 12-month questionnaires. Blinded researchers do not see these questionnaires until after primary outcome data are collected. Interviews at 6 and 12 months are carried out by a researcher who has not had any previous contact with the participant. Group allocation information for that participant is provided to the researcher before the interview so the correct interview guide can be used.

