### Trial design

A pragmatic, multisite, parallel, two-arm, assessor-blind, 1:1 superiority RCT comparing weight change at 12 months for the SMS intervention and active control groups, with mixed methods process evaluation, cost-effectiveness modelling, consent for future data linkage to longer-term health outcomes for mothers and babies, 24-month participant follow-up (ie, 12 months post intervention) and implementation consultations with stakeholders.

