### Strategies to improve adherence to interventions

Text message delivery is fully automated and centrally delivered via the LSHTM system which is intended to ensure treatment fidelity. Regular monitoring of the text message system is completed by the system developer and trial team members (Chief Investigator (CI) and clerical officer) to check the content of sent and received messages (eg, ensure web links are working, review spontaneous participant responses). Intervention engagement is assessed via text messages received from participants in response to the weekly weight prompt and the replies to bidirectional messages as described in the ‘Active control’ section, self-report items in questionnaires at 6, 12 and 24 months and qualitative interviews at 6 and 12 months.

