### Plans to promote participant retention and complete follow-up

Home visits are offered for data collection to facilitate women’s participation in research assessments, although visits can take place elsewhere if preferred by the participant. Visits are flexibly arranged for a date and time of convenience for the participant. At the end of each visit, the appointment for the next visit is scheduled if possible. Participants are sent reminders about scheduled visits at 1 month, 1 week and 1 day before the scheduled date and time. We attempt to collect data in a 2-week window on either side of the follow-up due date, that is, date ±2 weeks, but allow flexibility outside of this window when women are actively engaging with the research team to arrange the visit. Participants’ preferred methods of contact are documented and prioritised. Three contact attempts using different methods, for example, text, phone, email, are made to all women to confirm scheduled visits and following non-attendance to reschedule. Women who are unable to complete a visit with the researcher at 6 months are sent a link to complete the questionnaire (via Qualtrics email link). As a last resort, when all attempts to arrange a face-to-face visit at 12 (primary endpoint) and 24 months are unsuccessful, participants are asked to provide self-reported weight and complete a questionnaire (via Qualtrics email link). Participants are sent a £25 voucher at each trial time point (0, 6, 12 and 24 months; £100 maximum over 24 months) as a token of appreciation for the time committed to completing trial assessments. Participants lost to follow-up at one trial time point but who have not withdrawn are invited to attend future visits.

To maximise data completeness, site researchers follow-up on any non-returned questionnaires and check all received data forms/e-forms to document data queries (eg, missing data, invalid ranges) and any attempts made to resolve them, for example, clarify responses with the participant, using a data query log.

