### Data management

The hard copy of the CRF which records data at each time point including weight is the source data and requires sign-off by the completing researcher. For questionnaires, the hard copy or electronic record is considered the source data depending on mode of completion.

The Northern Ireland Clinical Trials Unit (NICTU) is responsible for developing and managing trial databases on validated and secure systems that back-up data, maintain audit trails of data changes and only allow password-protected access to designated trained team members. Screening and CRF data are entered into trial databases by site researchers and a 10% random quality control check of data completed by a different researcher. For Consolidated Standards of Reporting Trials (CONSORT) reporting, screening data includes anonymised summary information for women who do not proceed to randomisation. Paper questionnaires are scanned at site then the original posted to NICTU for data entry directly into the trial database.

Entered data are processed as per the trial-specific data management plan. Data queries are generated electronically by NICTU and site staff are required to respond to clarify data, provide missing information or make relevant amendments within the trial databases.

Online questionnaire completion is stored by the Qualtrics system on EU-based servers compliant with General Data Protection Regulation (GDPR) and exported by the Trial Manager for merging with the NICTU questionnaire database by the Trial Statistician (CC). Following completion of data collection, data are permanently deleted from Qualtrics.

Qualitative interview transcripts are anonymised and checked for accuracy against the audio recordings, then the recordings deleted.

A minimal amount of personal information (participant’s first name, mobile phone number and weeks postpartum at baseline) is entered into the randomisation system to allow delivery of text messages according to group allocation. Only designated trained team members have password-protected access to the randomisation system.

Text message engagement data are downloaded from the LSHTM system at the end of the intervention period in the form of all messages sent to and replies received from participants.

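### Assessor blinding of the 24-month weight and waist measurements is not secured, because site researchers handle the arm-specific 12-month questionnaires once the 12-month weight is taken

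*Protocol article*

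**What the plan says.** All references are to the protocol article.

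- **The claim.** Trial design describes "A pragmatic, multisite, parallel, two-arm, assessor-blind, 1:1 superiority RCT comparing weight change at 12 months", and the same sentence goes on to include the 24-month follow-up. Blinding states: "Researchers responsible for recruitment and collecting outcome data are blinded to group allocation". Neither statement carries a time limit.
- **The arm-specific form.** Under Blinding, "the clerical officer is responsible for preparing the group-specific 12-month questionnaires". The clerical officer is one of three roles listed there as not blind, with the chief investigator and the text-system developer.
- **The safeguard.** "Blinded researchers do not see these questionnaires until after primary outcome data are collected".
- **What happens to the forms next.** Under Plans to promote participant retention and complete follow-up, "site researchers follow-up on any non-returned questionnaires and check all received data forms/e-forms to document data queries", and they may go back to the woman to clarify her answers. Data management adds that paper copies are scanned at the site before they go to the trials unit (NICTU).
- **The later measurements.** Table 1 schedules weight and waist at 0, 6, 12 and 24 months. Data collection methods has the researcher take both.
- **The analysis.** Blinding states: "All statistical analyses are conducted blinded to group allocation until analyses of the 12 month data point are complete". Under Data management the online questionnaire data are "exported by the Trial Manager for merging with the NICTU questionnaire database by the Trial Statistician".

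**The concern.** Withholding the 12-month form until the primary weight has been taken makes sense only if seeing the form can reveal the arm. Once the restriction lifts, the staff who check and query those forms belong to the same group, site researchers, who carry out outcome visits. A site that follows the plan as written can therefore send a researcher who has learned a woman's allocation to measure her at 24 months.

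At stake is the credibility of the 24-month anthropometry. Weight change at 24 months is the first secondary outcome listed and carries the question of whether any effect lasts after the messages stop. Weight read from calibrated scales leaves little room for observer influence. Waist by tape depends more on the operator, so it is the more exposed measure.

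The second issue is the statistician's position. The blinding statement covers all analyses up to completion of the 12-month work, but the person who merges the questionnaire data is the trial statistician, who is not among the roles listed as unblinded.

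**Working it through.** The claim rests on no figure, so the check is to trace who sees the arm-specific form, and when.

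**Step 1. Does the form reveal the arm?** Blinding calls the 12-month questionnaires specific to the group, has an unblinded person prepare them, and keeps them from blinded researchers before the primary measurement. The article thus treats them as revealing.

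**Step 2. When does the protection end?** It ends when primary outcome data have been collected, that is, the 12-month weight. The sentence could be read per woman or for the whole trial:

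- *Per woman:* exposure can begin straight after her own 12-month measurement, about 12 months before her 24-month visit.
- *Whole trial:* Trial setting plans recruitment over 12 months from April 2022. The last 12-month visits then fall about 12 + 12 = 24 months after recruitment opens, which is when the first 24-month visits fall due. The remaining 24-month visits run over months 24 to 36. Most would still come after the restriction had lifted.

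The gap remains on either reading.

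**Step 3. Who handles the forms afterwards?** Site researchers check every form and e-form received and raise queries, and paper copies are scanned at site. Data collection methods also lets researchers help with paper completion at the visit or by telephone. Electronic queries raised by NICTU are answered by site staff.

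**Step 4. Who measures at 24 months?** The researcher. The article does not mention a separate assessor, or a rule that someone who has seen a woman's form must not measure her.

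**Step 5. The statistician's merge.** Weight is recorded in the case report form (Data management), so the primary analysis can run without questionnaire data. The 12-month diet, physical activity and infant-feeding outcomes cannot: the footnote to Table 1 places them in the self-report questionnaires. For women who answer online, the merge has to come before those 12-month analyses can be finished, while the blinding statement is still in force. The article does not say that arm-specific items are removed first.

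**Step 6. How many women?** Sample size calculation plans 119 completers at each of five sites. The stated targets reproduce: 119 / (1 − 0.30) = 170 and 119 / (1 − 0.37) = 188.9, rounded up to 189, giving 3 × 170 + 2 × 189 = 888. Planned completers are 5 × 119 = 595. This indicates how many women could be exposed; it is neither a count of returned questionnaires nor a measure of bias.

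**The case against.** The strongest reply is that the primary endpoint is safe and the rest is detail for documents not shown. Much of that stands.

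- The quoted safeguard protects the 12-month weight from disclosure through the 12-month form.
- The 24-month outcomes are secondary and treated as exploratory, and that stage depends on a decision by the steering committee and funder.
- Weight and waist follow standardised protocols, and unblinding events are recorded.
- The merge is described without timing or a list of fields, and a data management plan and a statistical analysis plan exist that may deal with masking. The randomisation sequence itself is withheld until the 12-month analyses are complete.

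Four stronger readings are tempting, and the article does not support them:

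- *The 24-month measurements are unblinded.* The article does not say that the person who checked a woman's form measures her at 24 months.
- *The 12-month analysis is unblinded.* The article does not say which fields reach the statistician or when, and the primary weight does not come from the questionnaire.
- *The 6-month questionnaire reveals the arm before the primary weight.* Table 1 lists message-satisfaction items at 6 months, and engagement is assessed through "self-report items in questionnaires at 6, 12 and 24 months and qualitative interviews at 6 and 12 months". Only the 12-month form is called group-specific, however, and the wording of the 6-month items is not shown.
- *A 6-month interviewer, told the allocation, may later measure the same woman.* The only stated restriction concerns earlier contact, so this is not expressly excluded. Read with the statement that outcome collectors are blind, it remains an inference, and it concerns about 50 interviews per time point.

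The reply does not remove the main point. The unlimited assessor-blind label and the time-limited safeguard both stand in this article, and the form handling it describes leads from one to the other.

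**Conclusion.** The point holds in a limited form. The procedures described do not secure assessor blinding of weight and waist at 24 months, although the trial is called assessor-blind without limit. This rests on two readings: that the group-specific form can reveal the arm, as the article's own safeguard implies, and that 24-month measurements come from the same pool of site researchers, since no other assessor is named.

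The statistician's merge is a secondary gap. It sits badly with the statement that all analyses are blind, because some 12-month outcomes need it, but it does not show that the primary weight analysis is unblinded.

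Up to about 595 women on planned numbers could be affected. The size and direction of any bias cannot be derived from the article. The 12-month weight measurement is not called into question.

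**What to change.** 1. Send the arm-specific pages of the 12-month questionnaire, for checking and scanning, to the clerical officer who is already unblinded or to NICTU data staff. Site researchers query only the arm-neutral sections. Help with completing the arm-specific pages would need the same route.
2. Where staffing allows, anyone who has seen a woman's allocation does not measure her afterwards.
3. Withhold arm-specific items from the statistician's file until the 12-month analyses are complete, and say so in the description of the merge.
4. Report by arm the unblinding events that are already being recorded.

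If the forms have already been handled at sites and this can no longer be done, limit the assessor-blind claim to measurements up to 12 months.

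The cost is a reallocation of checking among existing staff and a split export file, with slightly slower query resolution. Item 2 may be hard to meet at a site with few researchers, which is why it is conditional.

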### Emergency unblinding

Given the nature of the intervention, emergency unblinding is not required.

### Data collection, management and analysis

#### Data collection methods

The details and schedule of trial assessments (table 1) are based on the pilot RCT.^27^ Assessments take place at baseline (before randomisation), 6 months, 12 months (end of intervention period) and 24 months (12 months after intervention end).

Screening is completed according to the trial eligibility criteria and guided by and documented in a trial screening sheet.

Researchers, trained in data collection processes, collect outcome data during visits to women’s homes (or another venue of the participant’s choosing, eg, university/community venue). Height, weight and waist circumference are measured by the researcher using standardised protocols and calibrated scales. A hardboard is available to place under the scales on uneven surfaces. Baseline demographic information is collected by the researcher. Health service identification number is collected from any woman who provides consent for future data linkage. All remaining outcome data including health economic outcomes are collected via participant self-report questionnaires, either on paper (during the visit or a hard copy left with the participant along with a paid return envelope) or online (link to questionnaire hosted on Qualtrics survey software sent to participant and managed by the trial coordinating team in Queen’s University Belfast (QUB)), based on participant preference at each visit. Copies of the baseline and 12-month questionnaires are available in online supplemental appendix 3. Researchers offer any required assistance with paper questionnaire completion at the visit or via telephone.

Telephone interviews are conducted with approximately 50 women at each time point, with participants purposively sampled to include ethnic, geographical and sociodemographic diversity (ie, including a spread across trial sites, ethnicity, household income level, parity, mental health status, randomised groups and intervention engagement eg, those who have discontinued messages). Interviews follow a semistructured interview guide (available in online supplemental appendix 4) and a translator can be used when any woman would prefer to be interviewed in a language other than English.

Text message engagement data are captured by the LSHTM system, including all messages sent and received organised by participant ID and date.

If the intervention is shown to be effective at 12 months, we will invite a range of relevant stakeholders (eg midwives, GPs, PPI, commissioners, policy-makers) identified from research team and TSC networks to take part in interviews to explore factors relevant to engagement, scale-up and implementation.

Qualitative data are collected from participants and stakeholders using telephone/Microsoft teams interviews, which are audiorecorded and transcribed.

